**Methods/Design:**

This study was designed as three way randomized controlled trial with one year follow-up. Healthy individuals between 12 and 70 years of age, who were actively participating in sports and who had sustained a lateral ankle sprain in the two months prior to inclusion, were eligible for inclusion. After subjects had finished ankle sprain treatment by means of usual care, they were randomised to any of the three study groups. Subjects in group 1 received an eight week neuromuscular training program, subjects in group 2 received a sports brace to be worn during all sports activities for the duration of one year, and group 3 received a combination of the neuromuscular training program and a sports brace to be worn during all sports activities for the duration of eight weeks. Outcomes were assessed at baseline and every month for 12 months therafter. The primary outcome measure was incidence of ankle sprain recurrences. Secondary outcome measures included the direct and indirect costs of recurrent injury, the severity of recurrent injury, and the residual complaints during and after the intervention.

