### Sample size

As there is no scientific evidence on the combined effect of braces and neuromuscular training it is assumed that the effectiveness is comparable to the separate effect of braces or neuromuscular training alone[13]. Therefore, while reliable effect-sizes to calculate power are missing, a power analysis was done from the view of the intervention costs.

A recent Dutch study on ankle sprains and their prevention collected direct and indirect cost data related to ankle sprains [5]. Within this data a subgroup analyses of previously injured athletes revealed that the mean costs of a recurrent ankle sprain are €27 with an SD of €108. Home based neuromuscular training program costs are estimated at €25. Sports braces costs are estimated at €50. Consequently usual care costs are about €75 per recurrent ankle sprain. Based on an expected difference of €50 in costs (i.e, the cost difference between usual care and a neuromuscular training program), a total of 99 participants per group is needed. Taken into account an attrition rate of 20% this means that a total sample of 356 participants is required at baseline.

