### Recruitment of study population

Participants were recruited through the internet. Information on the study and a call for participation were available on the website: http://www.anklesbackincontrol.nl. The study was supported by the Dutch Association for Sports and Exercise Medicine (VSG), the Royal Dutch Physiotherapy Association (KNGF), the Dutch Orthopedic Association (NOV) and the Dutch College of General Practitioners (NHG). The participating organizations placed a hyperlink on their website. Hereby, individuals seeking medical information regarding ankle sprains in any of these sites came across this call for participants. Similar calls were placed on the websites of sporting associations of sports with a relatively high ankle sprain rate (e.g. soccer, volleyball, handball, basketball, korfball and tennis). Where possible existing electronic newsletters of sporting associations were used to contact potential participants directly. Next to the mentioned calls for participation on websites, we recruited actively by placing calls for participation on sports-related internet fora, as well as by electronic newsletters. This method of recruitment resulted in a sample of participants from a wide spectrum of different activities, sports and ages. Thus we created a sample representative to the Dutch sporting population. A similar recruitment strategy was successfully employed in a previous study on the same topic [15].

Recruitment of participants for the ABrCt study took place between April 2010 and May 2011. A total of 450 people were interested to participate in the ABrCt study and reacted on the call for subjects with a recent ankle sprain. A total of 18 athletes were classified as non-responders after a maximum of ten attempts to contact them through telephone or email failed. Of 432 people who were available for inclusion, 48 were excluded. Reasons for exclusion were: no return of baseline questionnaire (3), still undergoing treatment at the end of the inclusion period (5), no agreement on informed consent (2), vestibular complaints (2), non-recent ankle sprain (injury > 2 months before inclusion) (25), other serious injury (e.g. fracture of the ankle) (5) and private reasons (6). After completion of the baseline questionnaire and informed consent, 384 athletes were randomly assigned to the neuromuscular training group (n = 122), brace group (n = 126), and combined group (n = 136).

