### Statistical analyses

To evaluate the success of the randomisation, baseline values were analysed for differences between intervention group and control group, using a chi-square for categorical data and a student's t-test for numerical data.

All analyses were carried out according to the intention-to-treat principle. Cox-regression analysis was used to compare ankle recurrence risk between the intervention groups, using a significance level of P < 0.05. Other variables were checked for confounding and/or effect-modification and were adjusted for accordingly. Absence from sports was tested between groups using a Mann-Whitney test, since absence from sports due to an injury is not normally distributed [11].

Mean direct, indirect and total costs were estimated and compared between the three groups, both for the costs per subject in the injured population and for the costs per subject in the total population. Because costs are not normally distributed, 95% confidence intervals for the differences in mean costs were obtained by bias corrected and accelerated bootstrapping (2000 replications) [21]. Differences in costs and differences in ankle sprain recurrences were compared against the cheapest intervention (neuromuscular training) in a cost-effectiveness ratio, which estimated for each other condition the additional cost to prevent one ankle sprain recurrence. Confidence intervals for the cost-effectiveness ratio were calculated with bootstrapping, using the bias-corrected percentile method with 5000 replications. Uncertainty regarding the estimate of this ratio was expressed on a cost-effectiveness plane.

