### Recruitment

Web-based recruitment was very successful. Between april and december 2010 356 participants were recruited. Due to logistical problems intervention packages were never received by 28 participants. These 28 participants had to be excluded from the study. Therefore, an additional 28 participants were recruited in april and may 2011. This resulted in a final total of 356 included participants.

One of the drawbacks of this method of inclusion is that there is no control over the content of the provided usual care. Although ruling clinical guidelines are considered usual care, this does not necessarily mean that caregivers are actually following these guidelines. Inclusion of participants through a limited number of controlled (para-) medical caregivers would have decreased this problem. However, inclusion through such channels is problematic and in our experience results in lower inclusion rates than expected. Even so, in the current study we are looking for patients treated by a variety of (para-)medical caregivers. Meaning a relatively large number of different caregivers would need to be found, informed on the study, and controlled as to their given treatment. Looking at the required number of participants this would prove an undoable and unrealistic undertaking. Moreover, the proposed study is on the effectiveness of secondary preventive measures (e.g. extended treatment options) that are being applied after usual care. Full control over usual care and its content would have hampered external validity of this study. Finally, when inclusion would have been done by the caregiver this would mean that randomization would have needed to take place at the level of the caregiver. Such a clustered design would have further complicated the study design.

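### The baseline total of 356 does not cover the stated 20% attrition: 99 per group in three groups requires 372, and 356 tolerates only 16.6%

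*Protocol article*

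**What the plan says.** The article describes a three-group trial (Abstract, Methods/Design). Its Sample size section is based on costs: "Based on an expected difference of €50 in costs", with an SD of €108, leads to the statement that "a total of 99 participants per group is needed". The attrition step follows directly: "Taken into account an attrition rate of 20% this means that a total sample of 356 participants is required at baseline". That section gives no power, no alpha and no inflation formula. The only significance level in the article is in Statistical analyses, where the Cox regression is described as "using a significance level of P < 0.05".

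Two sections report how many people entered. Recruitment of study population gives 384 randomised: 122 to neuromuscular training, 126 to brace and 136 to the combination. The Recruitment part of the Discussion explains that 28 participants never received their intervention package and were excluded, that 28 more were recruited in April and May 2011, and that "This resulted in a final total of 356 included participants".

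**The concern.** An attrition allowance should ensure that the required number is still there after the assumed loss. That means dividing the required number by the retained fraction. Multiplying by one plus the loss rate gives too small a number, because the loss applies to everyone enrolled and not only to the number needed at the end. The article prints the per-group requirement, the number of groups, the attrition rate and the total, so the total can be checked without outside information.

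If the total is wrong, the article claims a safety margin that it does not have. A reader who later sees attrition of, say, 18% and compares it with the 20% allowed would wrongly conclude that the planned size had been kept. The figure also appears to have served as the recruitment target, since the included sample was brought back to exactly 356 after the exclusions.

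**Working it through.** **Inputs**

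- Required per group: 99 (Sample size)
- Groups: 3 (Abstract, Methods/Design)
- Attrition: 20% (Sample size)
- Stated baseline total: 356 (Sample size), equal to the final included total (Discussion, Recruitment)
- Difference €50 and SD €108 (Sample size)
- Randomised: 122, 126 and 136, total 384 (Recruitment of study population)
- Assumed, because not stated for this calculation: a two-sided t-test between two groups, with alpha either 0.05 or 0.05/3 (three pairwise comparisons)

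**1. The 99 per group.** With a difference of 50 and SD 108, a two-sided t-test at alpha 0.05 with 90% power needs 99.0 per group. The same test at alpha 0.05/3 with 80% power needs 99.1. Both readings fit the stated 99, and the article does not say which was meant.

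**2. The 356.**

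- Number needed at the end: 3 x 99 = 297
- Multiplying by one plus the loss: 297 x 1.2 = 356.4, which matches the stated 356
- Dividing by the retained fraction: 297 / (1 - 0.20) = 371.25; by group, 99/0.8 = 123.75, rounded up to 124, and 3 x 124 = 372

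**3. What 356 delivers.**

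- Remaining after 20% loss: 356 x 0.8 = 284.8, or 284.8/3 = 94.9 per group
- Largest attrition that still leaves 297: 1 - 297/356 = 16.6%
- Shortfall at baseline: 372 - 356 = 16, and 16/372 = 4.3%

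As a check, 372 x 0.8 = 297.6, which meets the 297.

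**4. Effect on power (difference €50, SD €108, two-sided t-test).**

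| Assumed alpha | 99 per group | 95 per group |
|---|---|---|
| 0.05 | 90.0% | 88.8% |
| 0.05/3 | 79.9% | 78.0% |

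**5. All 384 randomised.** A 20% loss in each group leaves 122 x 0.8 = 97.6, 126 x 0.8 = 100.8 and 136 x 0.8 = 108.8, that is about 98, 101 and 109. The total is 307.2, above 297, but the neuromuscular training group is still about one below 99. The sample described as final is 384 - 28 = 356.

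**The case against.** The strongest case on the other side is that this hardly matters. The gap is about four completers per group and one to two percentage points of power, recruitment closed in May 2011, and no design decision can now change. The power calculation is also remote from the trial's comparisons. The €50 is the cost difference between usual care and neuromuscular training, and usual care alone is not one of the three groups. The primary outcome is recurrence incidence, compared by Cox regression. In that analysis, participants lost partway can still contribute the time covered by their monthly questionnaires, so counting completers overstates the loss of information. All of this stands as a limit on the consequences. None of it makes 356 the right answer to the calculation the article sets out, because 356 x 0.8 falls below 297 however 356 was obtained.

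Three stronger readings go further than the article supports:

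- **That the plan multiplied by 1.2.** The match to 356.4 is close, but no formula is printed, so this remains an inference.
- **That power falls from a planned 90%.** The Sample size section states neither power nor alpha. The 0.05 is given for the Cox analysis, and an alpha of 0.05/3 with 80% power gives the same 99. Only the range in the table can be reported.
- **That analysing all 384 removes the shortfall.** An average of 384 x 0.8/3 = 102.4 per group hides the unequal allocation: the neuromuscular training group, which is the reference for the cost-effectiveness ratio, would still be just under 99. It would also require follow-up data on the 28 excluded participants, and the article does not say that such data exist.

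**Conclusion.** The stated baseline total is wrong by the article's own figures. The finding itself needs only the 99 per group, the three groups and the 20%. It does not depend on how 356 was derived, or on whether the cost-based rationale is sound. The power cost is small under either assumed alpha, and those power figures rest on a two-group t-test that the article does not specify. The point is therefore a correction to a published figure and to the attrition margin it implies. It is not evidence that the trial is materially underpowered.

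**What to change.** Correct the last sentence of the Sample size section in one of two ways:

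- state the requirement as 372 at baseline (124 per group), and note that the 356 included fell 16 short of it; or
- keep 356 and state that it preserves 99 per group only up to 16.6% attrition, leaving about 95 per group at 20%.

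The second is the more useful, since recruitment is over and 356 is what was included. With either option, state the power and alpha behind the 99, so that the effect of the shortfall can be given as one figure and not as a range. The fix should not rest on analysing all 384 as a way to restore the planned size in every group. The cost is one or two reworded sentences and no additional participants.

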### Recruitment of study population

Participants were recruited through the internet. Information on the study and a call for participation were available on the website: http://www.anklesbackincontrol.nl. The study was supported by the Dutch Association for Sports and Exercise Medicine (VSG), the Royal Dutch Physiotherapy Association (KNGF), the Dutch Orthopedic Association (NOV) and the Dutch College of General Practitioners (NHG). The participating organizations placed a hyperlink on their website. Hereby, individuals seeking medical information regarding ankle sprains in any of these sites came across this call for participants. Similar calls were placed on the websites of sporting associations of sports with a relatively high ankle sprain rate (e.g. soccer, volleyball, handball, basketball, korfball and tennis). Where possible existing electronic newsletters of sporting associations were used to contact potential participants directly. Next to the mentioned calls for participation on websites, we recruited actively by placing calls for participation on sports-related internet fora, as well as by electronic newsletters. This method of recruitment resulted in a sample of participants from a wide spectrum of different activities, sports and ages. Thus we created a sample representative to the Dutch sporting population. A similar recruitment strategy was successfully employed in a previous study on the same topic [15].

Recruitment of participants for the ABrCt study took place between April 2010 and May 2011. A total of 450 people were interested to participate in the ABrCt study and reacted on the call for subjects with a recent ankle sprain. A total of 18 athletes were classified as non-responders after a maximum of ten attempts to contact them through telephone or email failed. Of 432 people who were available for inclusion, 48 were excluded. Reasons for exclusion were: no return of baseline questionnaire (3), still undergoing treatment at the end of the inclusion period (5), no agreement on informed consent (2), vestibular complaints (2), non-recent ankle sprain (injury > 2 months before inclusion) (25), other serious injury (e.g. fracture of the ankle) (5) and private reasons (6). After completion of the baseline questionnaire and informed consent, 384 athletes were randomly assigned to the neuromuscular training group (n = 122), brace group (n = 126), and combined group (n = 136).

### Randomization procedure

After subjects had finished ankle sprain treatment by means of usual care, they were randomized to any of the three study groups. Stratification was based on type of usual care; (para-)medical treatment or no treatment/other treatment. Randomization took place at the end of usual care in order to minimize the chance of alterations in the treatment due to prior knowledge of the allocated intervention. As an example, a caregiver might decrease the amount of strengthening exercises when a patient was allocated to the neuromuscular training group. Even so, the other way around a caregiver might feel obliged to include additional strength and balance exercises when a patient is allocated to the brace group. Therefore, participants were asked to follow their usual treatment and/or rehabilitation program and received the allocated secondary preventive intervention after usual care had finished (and ideally before sports participation commenced).

### Interventions

The focus of this study is to evaluate the effectiveness and cost-effectiveness of secondary preventive measures after usual care for acute lateral ankle sprains. Therefore, after ankle sprain treatment and from the moment that sports participation commenced, participants received their allocated intervention protocol. Subjects in group 1 received an eight week neuromuscular training program, subjects in group 2 received a sports brace to be worn during all sports activities for the duration of one year, and group 3 received a combination of the neuromuscular training program and a sports brace to be worn during all sports activities for the duration of eight weeks.

Subjects allocated to the neuromuscular training group received a standardized eight-week unsupervised home based neuromuscular training program (Figure 2). This program has recently been proven effective for the secondary prevention of ankle sprains within a comparable setting [15].

**Figure 2 F2:**
[figure not shown]
**Home based neuromuscular training program, exercises A to F**.

All participants of the neuromuscular training group received the same balance board (Figure 3) for free. Furthermore general written and visual information on the duration and intensity of the program were provided. In addition, a website was created including basic information on the project and a section only accessible for each group's subjects. The exercise frequency was, with three training sessions per week, consistent throughout the full eight weeks (Table 1). The six exercises (A tot F) become more challenging as the program progressed (Table 2).

**Figure 3 F3:**
[figure not shown]
**Rock ankle exercise board, Avanco Sweden**.

**Table 1 T1:** Exercise schedule

**Exc**.	*Week 1*			*Week 2*			*Week 3*			*Week 4*			*Week 5*			*Week 6*			*Week 7*			*Week 8*		
	***1***	***2***	***3***	***4***	***5***	***6***	***7***	***8***	***9***	***10***	***11***	***12***	***13***	***14***	***15***	***16***	***17***	***18***	***19***	***20***	***21***	***22***	***23***	***24***

**A**	1	1	1	1	1	1	1	1	2	2	2	2	2	2	2	2	3	3	3	3	3	3	3	3
**B**	1	1	1	1	1	1	1	1	1	1	1	1	2	2	2	2	2	2	2	2	2	2	2	2
**C**	1	1	1	1	2	2	2	2	3	3	3	3	3	3	3	3	3	3	3	3	3	3	3	3
**D**	1	1	1	1	2	2	2	2	3	3	3	3	3	3	3	3	3	3	3	3	3	3	3	3
**E**	1	1	1	1	1	1	2	2	2	2	2	2	3	3	3	3	4	4	4	4	4	4	4	4
**F**	1	1	1	1	1	1	1	1	1	1	1	1	2	2	2	2	2	2	2	2	2	2	2	2

The content of each training session is shown vertically from session 1 to 24 (session numbers are printed bold). The exercises in each session are numbered A to F, the number (1 to 4) describes the difficulty level. Explanation of the difficulty level is given in Table 2.

**Table 2 T2:** Exercise difficulty level

Exc.	Difficulty level	Exc.	Difficulty level
**A**	1. on even surface	**E**	1. on even surface; with handheld
	2. on even surface; eyes shut		2. on even surface; without handhold
	3. on balance board		3. on even surface; eyes shut and without handhold
**B**	1. on high surface; with handhold		4. on balance board
	2. on high surface; without handhold	**F**	1. on even surface; walking
**C**	Same 3 levels as exercise A		2. on even surface; jumping
**D**	Same 3 levels as exercise A		

Subjects allocated to the brace group received an Aircast A60 Ankle Support brace for free (Figure 4). This is a semi-rigid ankle brace, specifically designed for use during sports. The design incorporates a sleek stabilizer located on either side of the ankle. This stabilizer is molded at a 60 degree angle to help guard against ankle sprains and prevent rollover. The light-weight anatomic design fits in athletic footwear. The brace is applied and adjusted with a single strap that securely holds it in place. The A60 is available in three sizes: small, medium, and large, with left and right models to guarantee optimal fit. Participants were encouraged to wear this brace during all sports activities for the duration of the entire 12 months follow-up.

**Figure 4 F4:**
[figure not shown]
**Aircast A60 Ankle Support brace**.

Subjects allocated to the combined group received both the standardized eight-week unsupervised home based neuromuscular training program and an Aircast A60 Ankle Support brace for free. Participants in this group were encouraged to wear the ankle brace during all sporting activities over a period of 8 weeks. The latter under the assumption that the neuromuscular program has achieved its preventive effect after 8 weeks, after which the use of a sports brace is considered redundant [13].

### Outcome measures

The primary outcome measure was incidence of ankle sprain recurrences, presented as the number of ankle sprain recurrences per 1,000 hours of sports participation. The following generic injury definition was used in this study: "An ankle sprain occurring as a result of sports participation or other daily activities and which causes one or more of the following:

• the subject has to stop the sports activity; and/or

• cannot (fully) participate in the next planned sports activity; and/or

• cannot go to work/school the next day; and/or

• needs medical attention (ranging from onsite care by e.g. first aid personnel, to personal care by e.g. physiotherapist, ER-doctor, or sports physician)."

Secondary outcome measures included the direct and indirect costs of recurrent injury, the severity of recurrent injury, and the residual complaints during and after the intervention.

This study has a one-year follow-up with measurements scheduled monthly for 12 months after baseline. All questionnaires and other forms were web-based and an invitation to fill out the questionnaires was sent to athletes by e-mail (with hyperlink), unless requested otherwise by the participant.

